### Intervention

#### Testing

Testing sessions for both the experimental and control groups will be conducted at baseline and every fourth week during the 12-week intervention period. Testing sessions every fourth week will help to establish the current physiological levels to develop the exercise prescription for the experimental groups.

Testing will be conducted in a university-based performance laboratory under the supervision of three exercise physiologists. Prior to completing the testing sessions, participants will be asked to refrain from food and drink (other than water) for 12 hours prior to the testing session, be well hydrated prior, avoid the use of alcohol, caffeine, and tobacco within 24 hours of testing, be well rested, avoid significant exertion or exercise the day of testing, and report any medication use prior to testing. Testing will occur as close to the same time of day as possible with the above directions prior to each testing session. Following the blood lipid profile testing (explained in detail later) and prior to the maximal exercise test, participants will be provided a small snack. The testing will be conducted as follows:Dietary analysis: participants will be instructed to not change their usual diets throughout the study and asked to complete a 3-day dietary intake recall including two weekdays and one weekend day to evaluate energy intake and the proportion of kilocalories from carbohydrates, protein, and fat.Anthropometric measurements: participants will be weighed on a calibrated, medical-grade scale to the nearest 0.01 kg and height will be measured using a stadiometer to the nearest 0.5 cm. Waist circumference will be measured by the narrowest horizontal circumference above the umbilicus and below the xiphoid process to the nearest 0.5 cm [4].Resting heart rate (RHR) and BP measurements: procedures for RHR and BP will follow standard guidelines [4]. In summary, participants will be required to sit for 5 minutes with sufficient back support, feet on the ground, and arms supported at heart level. Resting heart rate will be recorded by using a medical-grade pulse oximeter after the 5 minutes of seated rest. Blood pressure will be measured using a stethoscope and sphygmomanometer to determine left arm brachial artery BP on consecutive measure separated by 1 minute. The mean of the systolic and diastolic measures will be considered the resting BP.Fasting blood glucose and lipid measurements: all fasting lipid and blood glucose measurements will be analyzed using the Cholestech LDX system (Alere, Waltham, MA, USA), which has been shown to have excellent reproducibility [13, 14]. An optics check of the Cholestech LDX system will be completed at the beginning of each testing session. Participants will be asked to thoroughly wash hands with soap and rinse with warm water. The skin will then be wiped with an alcohol swab and allowed to dry. Using a lancet, the distal end of the third digit of the right hand will be punctured and a finger stick sample will be collected using a 40 μl capillary tube with blood flowing freely into the tube without milking the finger. The blood sample will then be extracted into a commercially available test cassette for analysis. Measurements of TC, HDL, LDL, triglycerides, and blood glucose will be obtained. Upon completion of the blood profile testing and data collection, blood samples will be disposed of based on standard biohazard procedures.VO_2_max and verification bout: participants will complete a modified Balke, pseudo-ramp graded exercise test (GXT) on a power treadmill. Participants will walk or jog at a self-selected pace with an increase in incline of 1% every minute until volitional fatigue. Heart rate and expired gas will be measured continuously using a heart rate monitor and a calibrated metabolic analyzer, respectively. Data will be analyzed following guidelines previously reported [5]. In summary, gas exchange data will be time averaged for every 15 seconds, VO_2_max will be determined by averaging the last two 15 second samples, and maximal HR will be the highest achieved HR during the GXT.

Since a verification procedure has been found to be effective in middle-aged and older adults to confirm VO_2_max [15], this procedure will be used to ensure participants have reached maximal capacity. The verification trial will be performed 20 minutes after the GXT as recommended elsewhere [16] and has been confirmed to be an effective procedure at altitude [17]. The verification bout will consist of a workload that is 105% of the maximal workload during the GXT (last fully completed stage) as this workload has been shown to be sufficient to elicit verification test durations of 2–3 minutes [15, 18] and will continue until volitional fatigue. Analysis of the verification bout will follow the same protocol as the GXT. ‘True’ VO_2_max will be considered to be attained if the GXT and verification bout are within ± 3% [15]. If participants are unable to reach VO_2_max, they will be asked to repeat the trial no sooner than 24 h later.

The control group will be asked to maintain their normal lifestyle activity habits. Therefore, in addition to the previously stated battery of testing, control participants will also complete the International Physical Activity Questionnaire (IPAQ) every fourth week at the testing session.

#### Biological variability and technical error

In order to establish criteria to categorize participants as responders or non-responders, the biological variability will be established to determine the TE. Therefore, from the pool of experimental research participants, 15 participants will be randomly selected based on when the referral or inquiry into the wellness program is received (i.e., participants 1, 3, 5, 7, etc. until 15 confirmed participants have been reached. If there are not 15 participants after the first round, then participants 2, 4, 6, etc. will be asked until the desired total of 15 participants is met). Participants will be asked to complete the baseline testing assessments twice within a 2-week period to determine the day-to-day biological variability. The biological variability will be combined with the typical error of the equipment utilized (sourced from the literature and company of the equipment) to determine the TE. More details related to the statistical approaches are located in the statistical analysis section.

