A notable factor that confounds current understanding of training response variability is the absence of a set definition in the literature of how to interpret a response (i.e. what classifies someone as a responder or non-responder). Indeed, criteria to determine incidence of response for changes in VO_2_max have included classifying a fixed proportion of the lowest training response [6], absolute changes in pre- to post-intervention values [7, 8], and a change of more than one standard deviation [9]. More recently, it has been proposed that technical error (TE), the combination of day-to-day biological variability and measurement error, should be applied to categorize response rate [10]. If these values are considered for each research cohort to report incidence of response, there would be greater consistency of reporting results within the literature to provide further insight on individual variability. Moreover, interpretation of the individual variability in training responsiveness is limited due in part to the standard practice of past studies only reporting group means and standard deviations. With reporting of only the mean and standard deviation, results of the intervention may not be applicable to all since there is a lack of understanding related to the individual variability of the investigation.

This trial will be the first investigation to address the incidence of response of VO_2_max and cardiometabolic risk factors following individualized and standardized cardiorespiratory fitness (CRF) training using a specific cohort-calculated TE as the criteria for response. Similarly, this will be the first study to evaluate the efficacy of modifying the CRF training intensity prescription for non-responsive participants (based on changes of VO_2_max) to investigate subsequent training responsiveness.

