#### Biological variability

Intraclass correlation (ICC) of variation, typical error and co-efficient of variation (CV) for VO_2_max, resting HR, resting BP, and fasting blood glucose, total cholesterol, HDL, and LDL will be calculated as described previously [26]. The CV will be combined with the measurement error of the testing to determine the TE. The TE will be used to categorize responders and non-responders. In summary, for all criteria tested the changes in pre- to post- intervention will be analyzed with responders having a change > TE and non-responders having a change that is ≤ TE.

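### The technical error combines a published equipment error with a test–retest CV that already contains it, so measurement error is counted twice against the protocol's own definition

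*Protocol article*

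**What the plan says.** The Background of the protocol article defines the quantity as "technical error (TE), the combination of day-to-day biological variability and measurement error".

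The section 'Biological variability and technical error' describes how it is obtained. Fifteen participants from the experimental pool "complete the baseline testing assessments twice within a 2-week period to determine the day-to-day biological variability". The same section continues: "The biological variability will be combined with the typical error of the equipment utilized". The equipment figure is to come from the literature and the equipment company.

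The 'Biological variability' part of the statistical analysis section computes an ICC, a typical error and a CV from the repeat tests, and then states: "The CV will be combined with the measurement error of the testing to determine the TE".

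TE has three uses. Determining it is the first of the four research outcomes in the Abstract. It is the only criterion for response, and so feeds the chi-squared comparison under 'Incidence of response'. Applied to VO2max, it decides who is asked to complete the second 12-week intervention.

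**The concern.** Repeating a test on the same equipment does not isolate biology. Each reading carries the random error of the analyser, cassette or cuff, so the within-person variation between the two sessions is biological variability and measurement error together. That is already TE in the Background's sense. The plan gives this total the name of one of its parts and then brings in the other part again from outside. The two sections that describe the calculation agree with each other, so this is not a slip in one sentence.

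At stake are the reported TE, which is a result in its own right, the response rates in both arms, and the number of people labelled non-responders and asked to train for another 12 weeks.

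**Working it through.** **Inputs.** From the documents: the definition of TE, the duplicate testing of 15 participants, the added equipment error, and a cut-off of 1 × TE on the percent change. The documents give no value for the CV or the equipment error and no combination rule, so there is no stated figure to reproduce. Every size below rests on assumed values.

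**1. What the repeat tests measure.** Let b be the biological SD and e the random equipment error, both in percent. The difference between two tests has variance 2(b² + e²), so

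typical error = SD of paired differences / √2 = √(b² + e²).

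With b = 4 and e = 3 this is √(16 + 9) = 5. A simulation with these values gave 5.00. The test–retest CV is therefore already TE as defined.

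**2. What the plan computes.** Write CV = √(b² + e²).

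- Root-sum-square: TE = √(CV² + e²) = √(b² + 2e²)
- Simple sum: TE = CV + e

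Both exceed CV whenever e > 0, so the direction does not depend on the rule.

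**3. Relative size, by the equipment share of the CV.**

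| e / CV | Root-sum-square | Sum |
|---|---|---|
| 0.25 | ×1.03 | ×1.25 |
| 0.50 | ×1.12 | ×1.50 |
| 0.71 (b = e) | ×1.22 | ×1.71 |
| 1.00 (limit) | ×1.41 | ×2.00 |

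**4. Illustration with assumed CV 5% and e 2–3%.**

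- Root-sum-square: √(25 + 4) = 5.39; √(25 + 9) = 5.83
- Sum: 5 + 2 = 7; 5 + 3 = 8
- Without the duplicate term: 5

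**5. Effect on participants with no true change.** A pre–post change has noise SD √2 × CV = √2 × 5 = 7.07%. The chance of being called a responder is 1 − Φ(TE / 7.07).

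| TE | Chance |
|---|---|
| 5 | 24.0% |
| 5.39 | 22.3% |
| 5.83 | 20.5% |
| 7 | 16.1% |
| 8 | 12.9% |

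**6. Effect on the classified response rate.** Assume also a mean gain of 8% and an SD of true gains of 5%. The observed change then has SD √(25 + 2 × 25) = 8.66%, and the share called responders is 1 − Φ((TE − 8) / 8.66): 63.5% at TE 5, 61.9% at 5.39, 59.9% at 5.83, 54.6% at 7 and 50.0% at 8. In a group of 20, the fall at e = 3 is 0.036 × 20 = 0.7 participants by root-sum-square, or 0.135 × 20 = 2.7 by sum.

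**The case against.** The strongest defence concerns the use of the cut-off. It is applied to a change score, whose noise SD is 1.41 × CV. On the assumed values that is 7.07%, so the root-sum-square TE of 5.4–5.8% is still below one noise SD, a sum of 7% about equals it, and only 8% exceeds it. A reader might infer from the double count that the cut-off is too strict for judging individual change. The documents do not support that: it is too high only relative to the Background's definition. Removing the duplicate term also has a price, shown in step 5. This part of the objection stands. It does not justify the duplicate term, which is not presented as an allowance for change-score noise and whose size follows a manufacturer's figure.

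Other points limit the finding:

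- The size is uncertain. The text says the two are combined, not how, and a condensed article may leave the formula to a fuller document. Under root-sum-square with a small equipment error the effect is modest. With 15 pairs, a CV of 5% has a 95% interval of about 3.7–7.9%, so an inflation of 0.4–0.8 points lies within TE's own sampling error. Unlike sampling error, though, the inflation always goes upward.
- A reader might infer a bias in favour of one arm. The same TE applies to both arms, so no one-sided bias follows.
- A reader might infer that the plan breaks its own criticism of earlier studies. The Background and Discussion fault those studies for borrowing biological variability, not equipment error, and this trial measures biological variability in-house.
- Equipment error might include parts that a two-week retest misses. A constant error on one device cancels in a pre–post change. Only drift beyond two weeks would be missed, and the protocol does not invoke it.

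**Conclusion.** The double count stands. As written, the calculation gives a TE above the protocol's own definition for any non-zero equipment error, whichever combination rule is used. This follows from the described procedure and needs no numerical assumption.

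The size does need assumptions: it is small under root-sum-square with a minor equipment share, and material under a simple sum. The consequences are an overstated cohort TE, lower classified response in both arms, and more participants entering the second 12 weeks. The repeated-measures and between-group analyses of VO2max as a continuous variable do not use TE and are unaffected.

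**What to change.** In 'Biological variability and technical error' and in the 'Biological variability' part of the statistical analysis section, set TE equal to the in-house test–retest typical error: the SD of the paired differences divided by √2, expressed as a percent CV, with no added equipment term. Report the manufacturer's error separately for information.

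An equivalent route is to subtract the equipment variance before recombining by root-sum-square. With CV 5 and e 3, √(25 − 9) = 4 and √(16 + 9) = 5, which returns the in-house value. Recombining by simple sum would not (4 + 3 = 7). In either case, write the formula into the text.

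The change needs no new data or participants. Its downside should be stated: on the assumed values, about 24% of participants with no true change would be called responders at 1 × TE. If a stricter cut-off is wanted, define it as an explicit multiple of TE that reflects the √2 noise of a change score, fixed before the data are analysed.

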#### Exercise intervention

After the completion of the baseline testing, participants will be randomly allocated to either the individualized or standardized arms at a 1:1 ratio using a computerized stratified minimization sequence. One of the primary investigators will have knowledge of the treatment groups to which participants have been allocated in order to interpret test results and prescribe target exercise intensities. However, this same investigator will not be involved in the implementation of the exercise training programs (to be completed by research assistants) in order to mitigate researcher bias. Participants will then be asked to come to the laboratory on Monday, Wednesday, and Friday to take part in the community wellness program and subsequent research. Upon arrival each day, participants will be asked to rest comfortably for 5 minutes in the seated position. Then, their resting BP and HR will be recorded. Following the resting measurements, participants will complete a 5-minute warm-up starting at a low and progressively increasing intensity until they are ready to begin their CRF exercise session. At this point, participants will be asked to stay within the designated HR (described in further detail below) outlined on their exercise log as determined based on their experimental group and week of experimental trial. At approximately 1/3 and 2/3 the total session time, an exercise physiologist or research assistant will record their current HR, rating of perceived exertion (scale 1–10), intensity of aerobic equipment, and any other pertinent notes. At the end of the CRF exercise session, the participant will be asked to complete a cooldown in which the exercise intensity is gradually reduced. While resistance training is not part of this proposed experiment, it is an integral part of the community wellness program and could be a confounding factor to the overall incidence of response. Therefore, all participants will be asked to complete the resistance training after the CRF training session is completed in order to have consistency among all participants. During the first 4 weeks, there will be no resistance training. During the next 4 weeks (week 4–8), there will be a learning and anatomical adaptation phase to resistance training in which proper technique and range of motion will be emphasized and participants will be acclimated to the resistance training machines. During the last 4 weeks (week 8–12) participants will complete one set of 8–12 repetitions on eight machine-based resistance training exercises and progress to two sets by the end of the 12th week [19].

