### Research aims

The objective of this research is to determine the incidence of response to VO_2_max after implementation of a standardized (%HRR) and individualized (based on first ventilatory threshold [VT1] and second ventilatory threshold [VT2]) approach to exercise prescription in a community wellness program for 12 weeks. The primary measurement outcome will be VO_2_max with secondary outcomes of total cholesterol (TC), high-density lipoprotein (HDL), low-density lipoprotein (LDL), triglycerides, blood glucose, and resting heart rate (HR) and blood pressure (BP). Thus, the main research aim is to determine whether an individualized exercise prescription decreases the incidence of non-response to CRF and cardiometabolic measurements compared to the standardized approach. Similarly, another primary research aim is to determine if changing the prescription of CRF intensity for a subsequent 12-week intervention elicits more responsiveness in previously categorized non-responders (based on VO_2_max responses). A key secondary aim of this research is to establish whether there are differences in the time course changes of VO_2_max and cardiometabolic risk factors between the experimental groups every fourth week during the 12-week intervention.

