
#### Determination of workload

For the standardized group, the workload will be determined based on %HRR and completed based on the following calculation:$$ \mathrm{H}\mathrm{R}\mathrm{R}=\left[\left(\mathrm{Maximal}\kern0.5em \mathrm{H}\mathrm{R}\hbox{-} \mathrm{Resting}\kern0.5em \mathrm{H}\mathrm{R}\right)\times \mathrm{Desired}\kern0.5em \mathrm{Percentage}\right]+\mathrm{Resting}\kern0.5em \mathrm{H}\mathrm{R} $$

For the individualized group, the workload will be determined based on ventilatory threshold values as previously described [5, 20] to determine VT1 and VT2. The criteria used for determining VT1 and VT2 will be a visual analysis of figures of time plotted against the relative respiratory variable – ventilatory equivalents of oxygen (VE/VO_2_) and ventilatory equivalents of carbon dioxide (VE/VCO_2_). Determination of VT1 will be an increase in VE/VO_2_ with no increase in VE/VCO_2_ and moving away from linearity of VE, whereas VT2 will be a simultaneous increase in both VE/VO_2_ and VE/VCO_2_. Calculations of HR values associated with ventilatory threshold (VT) values will be calculated prior to exercise sessions and with following HR ranges:Target HR > VT1 = HR range of 10 bpm below VT1 to the HR at VT1Target HR ≥ VT1 to < VT2 = HR range of 15 bpm above VT1 and below VT2Target HR ≥ VT2 = HR range of 10 bpm above VT2

Exercise volume will be prescribed based on energy expenditure per kg of body weight a week (kcal · kg^−1^ · week^−1^) to implement an isocaloric exercise volume (i.e., in terms of kilocalories [kcal] per kg a week) across individuals and groups. Previous research has found that energy expenditure ranging from 4 kcal · kg^−1^ · week^−1^ [21] to 23 kcal · kg^−1^ · week^−1^ [22–25] have positive effects on CRF and cardiometabolic responses to exercise. Therefore, this study will utilize a similar 12-week exercise protocol as previously described [5], while implementing a standardized isocaloric volume (kcal · kg^−1^ · week^−1^) instead of a designated time for each exercise session. Exercise progression will follow standard guidelines that have been previously established [4]. Figure 2 illustrates the exercise progression following baseline testing through the 12-week intervention for both experimental groups while Tables 1 and 2 show the SPIRIT study schedule for experimental and control participants, respectively.

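### The investigator who interprets the tests is told the allocation, although reading VO2max does not require it; the only stated bias safeguard covers training delivery

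*Protocol article*

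**What the plan says.** All references are to the protocol article.

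- **Who knows the arm.** Exercise intervention: "One of the primary investigators will have knowledge of the treatment groups to which participants have been allocated in order to interpret test results". The purpose given there is twofold: "in order to interpret test results and prescribe target exercise intensities".
- **The safeguard.** The next sentence, offered as the step against researcher bias, is that "this same investigator will not be involved in the implementation of the exercise training programs". Research assistants deliver the training.
- **The outcome.** Research aims: "The primary measurement outcome will be VO_2_max". Under Testing, it comes from a graded treadmill test at a pace the participant chooses, continued to volitional fatigue.
- **Who tests.** Testing: "Testing will be conducted in a university-based performance laboratory under the supervision of three exercise physiologists". The article does not say whether they know the arm. In training sessions, "an exercise physiologist or research assistant will record their current HR, rating of perceived exertion" and equipment intensity.
- **Double use of the tests.** Testing also says that the four-weekly sessions inform the exercise prescription.
- **Rules that limit discretion.** VO2max is the average of the last two 15-second samples. A verification bout at 105% of the maximal workload must agree within ±3%. If VO2max is not reached, the test is repeated at least 24 hours later.

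**The concern.** Two tasks are given to one unmasked person: reading the test and setting the training intensity. Only the second needs the allocation. The stated safeguard keeps that person out of the training sessions but does not touch the reading of the outcome, which is the task that could easily be masked.

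The trial compares a favoured approach (individualised) with a standard one. Its primary measure depends partly on how hard the participant pushes. Any drift by arm in how the VO2max test is conducted, repeated or read would enter the mean VO2max change. It would also enter the VO2max responder label, which decides who goes on to the second 12 weeks (Categorizing responders and non-responders; Modifying the prescription of non-responders). With about 16 analysed per arm (Sample size calculation), a small systematic drift is not negligible beside the sampling error.

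**Working it through.** The plan states no figure on this point, so the check is mainly a comparison of passages, task by task.

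| Task | Is allocation needed? | What the article says |
|---|---|---|
| Set the target heart rate | Yes | Done by the investigator who knows the arm |
| Derive VO2max | No: average of two 15-second samples | Interpreting test results is given to the same investigator |
| Verification pass or fail | No: numerical ±3% comparison | No decision-maker named |
| Decide on a repeat test | No | No decision-maker named; which value then counts is not stated |
| Conduct the maximal test | No | Three exercise physiologists supervise; masking not mentioned |
| Read VT1 and VT2 | No, but the article describes it for the individualised group only | "The criteria used for determining VT1 and VT2 will be a visual analysis of figures of time plotted" against ventilatory equivalents; no reader named |

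Two things follow.

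1. Weeks 4 and 8: the tests feed the next prescription, so the group must be looked up at some stage. It can be looked up after the reading is fixed.
2. Week 12: no first-stage prescription follows. The group is not needed until the VO2max result and the responder label exist; only then does it matter, to switch the non-responders.

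**Illustration of sensitivity only.** Apart from 16 per arm and the 5% level, every input here is assumed. Suppose there is no true difference, a t-test compares mean percentage change, and assessment or effort drift lifts one arm by *b* points.

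Noncentrality = *b* / (SD × √(2/16)), with 30 degrees of freedom and two-sided critical value 2.042. For SD 6 and *b* = 2: 2 / (6 × 0.3536) = 0.943, which gives a rejection probability of 0.150.

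| Assumed SD of change | *b* = 1 | *b* = 2 | *b* = 3 |
|---|---|---|---|
| 5 points | 0.085 | 0.195 | 0.376 |
| 6 points | 0.074 | 0.150 | 0.278 |
| 8 points | 0.064 | 0.105 | 0.177 |

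With 20 per arm, *b* = 2 gives 0.234 (SD 5) and 0.120 (SD 8).

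Responder rate = 1 − Φ((TE − mean)/SD). Assume a mean gain of 8%, SD 6 and a technical error (TE) of 5%. Without drift the rate is 1 − Φ(−0.50) = 69%. With a 2-point lift it is 1 − Φ(−0.83) = 80%. With SD 5 the move is 73% to 84%, and with SD 8 it is 65% to 73%.

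These figures show how a drift of a given size would act. They say nothing about whether a drift occurs or how large it is.

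**The case against.** **The prescriber has to know the arm.** This stands. The full sentence covers prescribing as well as interpreting, and interpreting could be read as part of prescribing. But the text as written gives this person the test results and the allocation together, and it describes no separate masked reading of the outcome.

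**Reading VO2max leaves little to judge.** This largely stands. The averaging rule and the ±3% criterion are numerical and identical in both arms, and pre-test conditions are standardised. An unmasked reader is therefore the weaker route to bias. What remains is effort: both bouts end at volitional fatigue, so a submaximal effort can recur in both and still agree within 3%.

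**An article condenses.** Silence about masking of the testing staff may be filled in a fuller document and is not counted here as an error. Giving the allocation to the person who interprets the tests is a stated choice, and so can be commented on.

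Several stronger readings are tempting but not supported:

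- *That this investigator runs the tests, encourages participants or decides on repeats.* The article assigns none of these to that person.
- *That the testing physiologists know the arm.* An exercise physiologist may record data in training sessions, but the article does not say that this is one of the three who supervise testing. Nor does a target heart rate on a log necessarily reveal which method produced it.
- *That blood pressure or VT1/VT2 readings distort the primary result.* Blood pressure is a separate outcome, VT1/VT2 are prescription inputs, and stage-two entry depends on VO2max alone. None of them is part of the measurement or calculation of VO2max change.

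**Conclusion.** The point holds in a limited form. The plan tells the allocation to the investigator who interprets test results, and its one stated safeguard concerns training delivery. Masked reading is feasible at every visit, and at week 12 there is no first-stage reason against it. This leaves an avoidable risk of bias that is modest and of unknown size. It lies mainly in effort during a test ended at volitional fatigue and in how repeat tests are handled, and less in the arithmetic of reading VO2max.

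A reader might infer that the primary result will be biased or that its type I error is already inflated. The article does not show that. The 11–20% range for a 2-point drift depends on an assumed drift and an assumed SD of change. The improvement is inexpensive and worth making, but the design does not fail without it.

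**What to change.** Amend the Exercise intervention section as follows.

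1. VO2max, verification pass or fail and maximal heart rate (and VT1/VT2, where read) are derived under a coded ID and locked before the group is looked up to calculate the target heart rate.
2. At week 12 the group is withheld from the reader until the VO2max result and the responder label are locked.
3. All maximal and verification tests use one fixed encouragement script, and testers are not told the arm where existing staffing allows.

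The cost is protocol wording, coded file handling and slightly more reading work. Items 1 and 2 need no additional visits or staff. The article gives no rostering figures, so full masking of testers is set out as a preference and not a requirement. Having a tester who did not supervise that participant's training would not by itself mask anyone.
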